## Abstract

**Background:**

Gaps in maternal and child health services can slow progress towards achieving the Sustainable Development Goals. The Management and Optimization of Nutrition, Antenatal, Reproductive, Child Health & HIV Care (MONARCH) study will evaluate a Continuous Quality Improvement (CQI) intervention targeted at improving antenatal and postnatal health service outcomes in rural South Africa where HIV prevalence among pregnant women is extremely high. Specifically, it will establish the effectiveness of CQI on viral load (VL) testing in pregnant women who are HIV-positive and repeat HIV testing in pregnant women who are HIV-negative.

**Methods:**

This is a stepped-wedge cluster-randomised controlled trial (RCT) of 7 nurse-led primary healthcare clinics to establish the effect of CQI on selected routine antenatal and postnatal services. Each clinic was a cluster, with the exception of the two smallest clinics, which jointly formed one cluster. The intervention was applied at the cluster level, where staff received training on CQI methodology and additional mentoring as required. In the control exposure state, the clusters received the South African Department of Health standard of care. After a baseline data collection period of 2 months, the first cluster crossed over from control to intervention exposure state; subsequently, one additional cluster crossed over every 2 months. The six clusters were divided into 3 groups by patient volume (low, medium and high). We randomised the six clusters to the sequences of crossing over, such that both the first three and the last three sequences included one cluster with low, one with medium, and one with high patient volume.

The primary outcome measures were (i) viral load testing among pregnant women who were HIV-positive, and (ii) repeat HIV testing among pregnant women who were HIV-negative. Consenting women ≥18 years attending antenatal and postnatal care during the data collection period completed outcome measures at delivery, and postpartum at three to 6 days, and 6 weeks. Data collection started on 15 July 2015. The total study duration, including pre- and post-exposure phases, was 19 months. Data will be analyzed by intention-to-treat based on first booked clinic of study participants.

**Discussion:**

The results of the MONARCH trial will establish the effectiveness of CQI in improving antenatal and postnatal clinic processes in primary care in sub-Saharan Africa. More generally, the results will contribute to our knowledge on quality improvement interventions in resource-poor settings.

**Trial registration:**

This trial was registered on 10 December 2015: www.clinicaltrials.gov, identifier NCT02626351.

**Electronic supplementary material:**

The online version of this article (10.1186/s12913-018-3404-3) contains supplementary material, which is available to authorized users.

## Background

South Africa has made considerable gains in improving prevention of mother-to-child transmission of HIV (PMTCT) services coverage since being identified as a Global Plan Priority country in 2009 [1]. In 2012, nearly 4 million women in the country lived with HIV and antenatal HIV prevalence was 30% [2]. The PMTCT Cascade of Care (CoC) refers to key steps in the clinical pathway from early diagnosis of HIV in pregnancy/postpartum to achieving long-term maternal HIV virologic suppression on antiretroviral therapy (ART), retention-in-care, and early infant diagnosis and treatment [3]. Leakages in the PMTCT care cascade hinder progress towards eliminating paediatric HIV and protecting maternal and child health.

Among pregnant women who are HIV-positive, HIV viral load (VL) testing is critical to judge the clinical performance of ART and to prevent vertical transmission of HIV from mother to child [4, 5]. Vertical transmission risk increases with maternal VL [6, 7]. VL testing can identify virologic failure early, leading to timely interventions such as adherence counselling, resistance testing and treatment switches, and enhanced antiretroviral prophylaxis for HIV-exposed infants [8]. Moreover, VL testing is important because large proportions of pregnant women on ART are failing virologically (by some estimates 20–40% [9, 10]). The South African National PMTCT guidelines recommend universal ART for pregnant women who are HIV-positive and regular VL testing to monitor the clinical performance of ART [11]. However, in many communities in South Africa and other sub-Saharan African countries the majority of pregnant women on ART, and non-pregnant women and men, do not receive regular VL tests [12–15].

Repeat HIV testing of pregnant women who are HIV-negative is important because HIV incidence in pregnancy is high in many countries [16]. In South Africa, HIV incidence in pregnancy and postpartum is estimated to be above 4% [10, 16]. Since VL increases markedly shortly after infection, the risk of MTCT is particularly high among recently infected women [17]. Early diagnosis of HIV and initiation of ART are thus critical to ensure that MTCT is eliminated, but this requires pregnant women who are HIV-negative to be re-tested at regular intervals [18]. The South African National PMTCT guidelines thus recommend pregnant women who are HIV-negative to be tested in three-monthly intervals after the initial HIV test during the first antenatal visit [11]. However, in South Africa and other countries in sub-Saharan Africa large proportions of pregnant women who are HIV-negative do not receive repeat HIV tests [17, 19, 20].

In addition to the need for improvements in early diagnosis of HIV and regular VL monitoring of ART in antenatal care, adherence to clinical guidelines and quality of care continue to be major challenges following delivery in many countries [21, 22], undermining the delivery of effective postnatal care to mothers and children including ART, safe infant feeding and postnatal contraception.

One important approach to improving quality of care in the health sector is Continuous Quality Improvement (CQI) [23, 24]. Several features of CQI make it an attractive choice to improve quality of care and adherence to clinical guidelines in pregnancy-related care in sub-Saharan Africa. First, CQI uses time-tested and robust management techniques to diagnose quality problems, develop solutions and monitor progress. These techniques can be adapted to improve many different processes and healthcare functions, depending on clinical contextual needs and opportunities for improvement identified with real-time data [23, 24]. Second, CQI empowers health workers to develop approaches and take actions to improve quality of care on an ongoing basis. CQI mentors work with local clinic staff to facilitate the development of solutions to quality of care shortcomings that the staff identify as best suited to their local contexts. Third, CQI works within existing resource constraints and does not require large long-term investments to ensure sustained improvements in quality of care [25].

Several randomized controlled trials have demonstrated that CQI initiatives can be successful in improving quality of hospital care in resource-rich countries [26–28]. However, despite major CQI initiatives in primary care in several sub-Saharan African countries [29–33], rigorous scientific evidence on CQI effectiveness in these settings is largely lacking.

The MONARCH stepped-wedge cluster RCT will for the first time establish the effectiveness of an intervention to improve VL testing in pregnant women who are HIV-positive and repeat HIV testing in pregnant women who are HIV-negative in primary care clinics in rural South Africa.

More broadly, the trial will contribute to our understanding of the effectiveness of CQI in improving the quality of antenatal and postnatal care and add to the scarce but growing evidence on the effectiveness of CQI as an approach to improve quality of care in sub-Saharan Africa [34, 35]. This evidence is important because several governments in sub-Saharan Africa are using CQI to improve quality of care in public-sector healthcare provision [29–33].

### Primary and secondary endpoints

Our primary endpoints are (i) viral load testing among pregnant women who are HIV-positive and (ii) repeat HIV testing among pregnant women who are HIV-negative. Our secondary endpoints are:(i)Patient experiences of healthcare quality among all pregnant women(ii)Maternal health outcomes including:Postnatal care attendance within 6 weeks postpartum among all pregnant womenMaternal retention in HIV care among women who are HIV-positiveART utilization among women who are HIV-positiveMaternal HIV virologic suppression among women who are HIV-positiveHIV seroconversion in pregnancy among women who are HIV-negative(iii)Infant health outcomes including:Mother-to-child transmission of HIVNevirapine prophylaxis for HIV-exposed infantsInfants with weight, length, and head circumference measured(iv)Maternal knowledge and uptake of key services including:HIV servicesContraceptive servicesExclusive breastfeeding(v)Healthcare provider job satisfaction and motivation

## Methods and design

### Study setting and CQI implementation

The study setting is rural KwaZulu-Natal, South Africa, in the community participating in the population health research carried out by the Africa Health Research Institute (AHRI) which was previously known as the Africa Centre for Health and Population Studies. AHRI is located within a 438 km^2^ area in the mostly rural Hlabisa sub-district of northern KwaZulu-Natal (Fig. 1). As a Wellcome Trust-Howard Hughes Medical Institute major overseas programme, the AHRI Population Intervention Platform Surveillance Area (PIPSA) South has collected comprehensive longitudinal population and HIV surveillance data on consenting individuals ≥15 years old (approximately 90,000 people in 11,000 households) since 2003. HIV prevalence amongst women of reproductive age is ~ 37% [36]. Overall fertility has been stabile since 2000, at about three children per woman, with an average of 2200 live births per year [37].

**Fig. 1 Fig1:**
[figure not shown]
The Africa Health Research Institute study site at Somkhele. Location of the MONARCH study. Based on: Tanser et al. 2008 [46]

There are 6 nurse-led Department of Health (DoH) primary healthcare clinics (PHCs) of varying size within the geographic bounds of PIPSA South. The clinic immediately outside the PIPSA South geographic bounds located in the market town of Mtubatuba, adjoins a major highway and is often visited by PIPSA residents regardless of proximity. It was thus added to the 6 clinics within PIPSA South for this study. Oversight of these 7 clinics is led by the local primary level sub-district hospital, Hlabisa Hospital. Medical officer support is provided weekly where possible.

The CQI intervention in this study was delivered by the University of KwaZulu-Natal (UKZN) Centre for Rural Health (CRH) CQI specialist team who travelled from Durban, KwaZulu-Natal, to the study site. They worked collaboratively with PHC staff to implement changes in clinical practice through training and mentorship using real-time clinic data. The CRH team consisted of two isiZulu-speaking South African professional nurses (CRH CQI mentors) and a data capturer who carried out field activities, with close support from an Improvement Advisor (a consultant obstetrician with CQI experience), a Scientific Advisor and a data manager. CQI field activities for the entire project were scheduled in advance of the first intervention step and are described in detail below.

### Study design

The study, a stepped-wedge cluster RCT, was carried out from 15 July 2015 to 30 January 2017, at the 7 DoH PHCs described above: Mtubatuba, KwaMsane, Mpukunyoni, Somkhele, Machibini, Esiyembeni and Gunjaneni. All clusters crossed over from control to intervention exposure according to the stepped-wedge study design (Fig. 2). The six clusters were randomised to the calendar sequences of crossing over. The stepped-wedge study design was selected because (i) it was considered unethical to withhold the intervention from some clinics as CQI has known efficacy in resource-rich settings; (ii) the participation of all clinics both during the control and the intervention exposure state was thought to be better if it was known that during the course of the trial all clinics would receive the intervention; (iii) the field implementers of CQI were a small team of three people, making simultaneous rollout in all clusters impracticable; and (iv) it allows adjustment for secular trends in outcomes. Data collection occurred at all 7 DoH PHCs and Hlabisa Hospital maternity ward as the majority of deliveries from the sub-district occur at Hlabisa Hospital.

**Fig. 2 Fig2:**

The MONARCH stepped wedge study design. Clinics provided baseline (pre-intervention) data until each rolled over to the intervention in random order. All clinics provided data continuously throughout the study period. Baseline data collection across all clinics occurred from 15 July 2015 to 28 September 2015 (Step 0). As data extraction on antenatal visits was retrospective from the point of delivery, the baseline observation period covered an additional ~ 6 months for the first recruited participants – thus Step 0 covered a duration of ~ 8 months

### Eligibility criteria

#### Clusters

The clusters were pre-defined and included the 6 PHCs within the PIPSA South area plus Mtubatuba clinic. Antenatal care providers within clusters participated in the CQI activities based on availability. Efforts were made to recruit providers in leadership roles (e.g. Operational Managers, Professional Nurses) to increase likelihood of sustainability of the intervention and dissemination of skills. Based on clinic size (and staffing) approximately five participants from each clinic constituted a facility-level CQI team, which ideally included at least one person in a leadership position.

#### Individuals

All women aged 18 years or older were overall eligible for outcome and exposure assessment at three time points independent of previous or prospective recruitment status: at delivery, at the 3–6 day postnatal visit, and at the 6-week postnatal visit. Recruitment occurred continuously at all clinics and Hlabisa Hospital over the entire study period regardless of the clinic’s randomisation status. Women who had just delivered a baby at Hlabisa Hospital or any of the 7 study clinics were recruited for outcome and exposure assessment if they had attended any of the 7 study clinics for antenatal care (ANC) or resided in PIPSA South during their pregnancy. Consenting women attending a 3–6 day or 6-week postnatal visit at a study clinic with their infant (aged < 8 days or 5–8 weeks respectively) were recruited regardless of ANC clinic attended or where they resided during pregnancy.

### Procedures

#### Conceptual framework

We hypothesized that this CQI intervention would bring about the desired changes in clinical processes by providing a supportive and motivating environment alongside real-time data to PHC-level healthcare providers. The CRH team supported PHC staff to implement simple workable solutions to gaps identified through collaborative root-cause analyses. Furthermore, CQI may have increased job satisfaction and empowerment through reduced workload and better patient outcomes. Implicit in these assumptions were staff availability to participate in CQI activities and the ability to continue normal clinical duties in parallel to CQI activities.

#### Intervention package

Each intervention step was of 2 months’ duration with a 2-month pre-exposure data collection period and a 4.5-month endline (Fig. 2). We refer to the first 2-month intervention step as the ‘transition’ phase – this was the start of the intervention, in which ‘intensive’ CQI was delivered. The maintenance phase occurred after this transition phase for each cluster and included support and maintenance CQI visits in approximately monthly intervals. Visit types and planned activities are described in Table 1.

**Table 1 Tab1:** Description of CQI intervention visit types and activities

Study phase	Visit type	Description of activities
Intensive CQI (transition)	Induction	• Introduction to the CRH QI team • Situational analysis with preliminary appraisal of local clinic processes and pre-exposure data collection using facility data sources such as registers • Training of facility staff by CRH CQI mentors on CQI methodology and tools
	Intervention	• Mapping clinic processes and establishing priorities for process improvements through bottleneck and root-cause analyses with standardized CQI tools such as process maps, fishbone diagrams, initiation of PDSA cycles and run charts • Implementing changes and monitoring progress through PDSA cycle reviews and run charts
	Support	• Mentorship, support and ongoing assistance to monitor progress and review changes via iterative PDSA cycles and run charts • Considering to adopt the implemented changes (Change Package)
Maintenance	Support	• Mentorship, support and ongoing assistance are provided to monitor progress and review changes via iterative PDSA cycles and run charts • Considering to adopt the implemented changes (Change Package)
	Maintenance	• As for Support visits
	Action Learning Session	• Sharing change ideas and experiences with other facilities already randomised to the intervention

*CQI* Continuous Quality Improvement, *CRH* Centre for Rural Health, *PDSA* Plan-Do-Study-Act

CQI field activities for the entire project were scheduled in advance of the first intervention step. Clinic-based CQI activities occurred over 3 days of a given week, and administrative work scheduled for a separate day each week. CQI tools and principles (Tables 1 & 2) included Action Learning Sessions at the end of each transition phase to consolidate skills and share experiences. The intervention was based on the Institute for Healthcare Improvement (IHI) breakthrough collaborative CQI model [38]. Given time constraints imposed by the study design, activities mainly targeted the primary endpoint indicators: repeat HIV screening and HIV viral load (VL) testing according to South African PMTCT guidelines (Additional file 1: Text S1). Additional study endpoint indicators were addressed as time permitted.

**Table 2 Tab2:** Description of CQI tools used in the intervention

CQI tool	Description
Process map	A map of clinic processes relating to a specific activity from the time a patient walks into the clinic A map, including waiting times and waiting site, is created for each activity as there may be differences in the process based on clinical need (e.g. a patient who is HIV-positive with tuberculosis co-infection versus a patient who is HIV-positive without tuberculosis). Mapping identifies areas for improved process efficiency, thereby reducing clinical workload and patient waiting times.
Run chart	A display of real-time data on target indicators The run chart is the essence of the ‘data-driven’ approach of CQI. Target indicators, or process indicators, are selected during the early stages of CQI implementation, for monitoring throughout the period of CQI activities. Facility staff can observe the results of changed activities using their own data in real-time on the so-called run chart. The run chart facilitates motivation and buy-in.
Fishbone diagram	A diagrammatic representation of factors contributing to a specific clinical endpoint – a ‘cause and effect’ diagram
PDSA cycle [44]	A representation of the process of change In the Planning stage, facility staff (guided by CRH CQI mentors) plan how to implement change targeting a specific endpoint (Plan). This is followed by actual implementation (Do) and review of progress and challenges (Study). The change becomes embedded in normal practice if implementation was successful, or generates a different method of implementation (Act).

*CQI* Continuous Quality Improvement, *CRH* Centre for Rural Health, *PDSA* Plan-Do-Study-Act

Prior to transition-phase CQI activities, a 2-week lead-in period (approximately 4 visits) was planned, to introduce the newly randomised cluster to the CRH team and CQI concepts. A standardized ‘dose’ of intensive CQI of ~ 19 visits, was planned for each transition step. A schedule of monthly follow-up (CQI maintenance) visits was also planned thereafter and varied by cluster due to order of randomisation.

Efforts to prevent cross-contamination whilst enabling buy-in for sustainability of CQI were made: only randomised clinics were invited to attend Action Learning Sessions, and PHC supervisors were excluded from these events during the intervention period (unlike ‘real-world’ implementation of CQI) as they supervise multiple clinics. However after the final transition step was complete, a final joint Action Learning Session with staff from all 7 clinics, PHC supervisors, sub-district and district DoH staff was held. In order to reduce bias the AHRI study investigators (evaluators) refrained from intervening in CQI clinic processes, although some operational co-involvement was required (e.g. introducing the CRH team to clinic staff).

#### Comparator

During the control exposure state, maternal and child healthcare providers continued providing DoH standard of care to ANC and PNC attendees as usually implemented. The South African maternal and child health strategic plan outlines the maternal package of services to be provided, including basic antenatal care. Usual training for staff involves weekly 1 hour in-service training on current evidence-based guidelines applied to primary healthcare services and may include training on ANC or PNC. The usual training, however, does not contain a mentoring component and is not a data driven process to evaluate the implementation of evidence-based guidelines. Additional background details on DoH standard of care are provided (Additional file 1: Text S1).

#### Data sources

All eligible women had their Maternity Case Record (MCR) photographed at delivery, excluding the intrapartum section, based on UKZN Biomedical Research Ethics Committee waiver of requirement for consent to access routine DoH data. All consenting women were interviewed at delivery and their infant’s Road-to-Health Booklet (RtHB) photographed. The structured interview covered themes on demographics, satisfaction with services, obstetric history, pregnancy intention, healthcare expenditures, access to care, and knowledge (infant feeding and HIV). At the 3–6 day and 6-week postnatal visits all consenting women were interviewed and their infant’s RtHB photographed. The structured interview at the 3–6 day visit was identical to the delivery visit. The 6-week structured interview covered themes on demographics, satisfaction with services, knowledge and uptake of services (HIV, PMTCT services, adherence to ART, contraception, self-reported infant feeding practices), healthcare expenditures, and access to care. All questionnaires contained questions in English with isiZulu translations and were conducted in isiZulu.

Structured interviews of consenting healthcare providers at the 7 study clinics were undertaken in English covering themes on job satisfaction, motivation and antenatal care practices, at study mid-point and study end.

Process evaluation data sources included semi-structured healthcare provider interviews undertaken in English, and detailed CQI implementation records from CRH for each PHC. The latter included actual visit dates, visit type, and descriptions of the successes and challenges the CRH CQI mentors encountered in implementing CQI.

Data collection from clusters commenced on 15 July 2015 and concluded on 30 January 2017. Each cluster contributed pre-exposure data until rolled over to the CQI intervention. Data collection continued from all clusters throughout the study until project end, providing pre-exposure, transition phase and post-exposure outcome data on all clusters.

As women were recruited at delivery or thereafter starting on 15 July 2015 - with retrospective capturing of their routine antenatal care data – the 2-month baseline data collection period contributed an additional observation period of ~ 6 months, resulting in a total data collection period of ~ 19 months and total observation period of ~ 25 months. The final post-exposure period (after all clusters had received the intervention) was 4.5 months (Fig. 2).

Eleven data clerks trained in International Conference on Harmonisation (ICH) Good Clinical Practice (GCP) guidelines were based at either Hlabisa Hospital or the 7 PHCs throughout the study. All data collected in clinics and Hlabisa Hospital, including cameras, were returned daily to the AHRI data centre for secure storage and capturing. A data capturing team of five trained in ICH GCP, including research nurses and quality controllers, captured clinical and laboratory data from digital photographs of MCRs and infant RtHB, and all information from structured questionnaires onto a REDCap™ study database [39].

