#### Randomisation and blinding

Each clinic was a cluster, with the exception of the two smallest clinics, which jointly formed one cluster. After a baseline data collection period of 2 months, the first cluster crossed over from control to intervention exposure state on 29 September 2015; subsequently, one additional cluster crossed over every 2 months (Fig. 2). The six clusters were divided into 3 groups by patient volume (low, medium and high). To increase the likelihood that the sample sizes in intervention and control exposure states were similar, and to improve balance, we then randomised the clusters to the six calendar sequences of crossing over, such that both the first three and the last three sequences included one small, one medium, and one large cluster. A senior biostatistician performed randomisation for all clusters prior to the first intervention step. All study implementers, evaluators and clinic health workers were blinded to the initial randomisation status. Two weeks prior to each scheduled intervention step crossover date, the custodian of the randomisation list (AHRI Chief Information Officer) revealed the randomised cluster to the AHRI study team. The AHRI study team then introduced the CRH team to the randomised cluster for CQI training to commence.

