#### Statistical analysis

The data will be analyzed by intention-to-treat (ITT). For ITT analyses, patient outcomes will be analyzed by the exposure status of the clinic attended at the first antenatal booking visit, independent of later clinic switches. We will analyse the CQI effect using mixed effects generalized linear regression models. In the main analysis, we will include a fixed effect for the time step and a random effect for clinic, following Hussey and Hughes [41], as well as adjust for clustering of standard errors at the clinic level. For the analyses of our two primary endpoints, which are binary, we will use modified Poisson regression [42] within the generalized linear regression framework. Our main results will thus be expressed as risk ratios. In sensitivity analyses, we will adjust for patient pre-exposure characteristics, and we will assess effect modification by secular time and time since intervention start in a clinic [43]. Stata (version 15.0, StataCorp, College Station, Texas) will be used for all analyses.

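### Provider job satisfaction and motivation rest on a single randomised comparison of six clusters, so this secondary endpoint should be labelled exploratory

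*Protocol article*

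**What the plan says.** The Primary and secondary endpoints section of the protocol article lists, as item (v), "Healthcare provider job satisfaction and motivation". Under Data sources, providers at the seven clinics are interviewed "covering themes on job satisfaction, motivation and antenatal care practices, at study mid-point and study end"; no structured provider interview is scheduled at study start. The same section then describes data collection in all clusters as "providing pre-exposure, transition phase and post-exposure outcome data on all clusters".

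On timing, the Study design section says the trial "was carried out from 15 July 2015 to 30 January 2017", and Randomisation and blinding says "the first cluster crossed over from control to intervention exposure state on 29 September 2015; subsequently, one additional cluster crossed over every 2 months". The order was randomised under a restriction, "such that both the first three and the last three sequences included one small, one medium, and one large cluster".

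On analysis, the Statistical analysis section says "We will analyse the CQI effect using mixed effects generalized linear regression models", with a fixed effect for time step, a random effect for clinic and standard errors clustered by clinic. No model or test level is given specifically for the provider endpoint. The 5% level appears only in the Power calculation, for the two primary endpoints.

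**The concern.** A stepped wedge earns its causal claim from clusters seen in both states, and from rounds in which some clusters are exposed while others wait. For the women's outcomes there are many such rounds. For the provider endpoint there is one, because by the second interview every cluster is exposed. Data sources nevertheless states without exception that all clusters supplied pre-exposure data, and the only effect model described is the general one.

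If that model is run on two provider rounds and yields a small p-value, a reader would take it as randomised evidence of the same kind as the primary results. The Conceptual framework says CQI works partly through a supportive and motivating environment, and may raise job satisfaction. A chance positive could be read as support for that account, and an uninformative null as evidence against it.

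**Working it through.** The document gives no sample size, power or test level for this endpoint, so there is no stated figure to reproduce.

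**1. Exposure at the mid-point.** From 15 July 2015 to 30 January 2017 is 565 days, so the calendar mid-point is about 22 April 2016. Two-monthly crossovers from 29 September 2015 fall near 29 November, 29 January, 29 March, 29 May and 29 July. Four precede 22 April. The fourth does so by only about 24 days and is therefore still in its two-month transition phase. The split is 4 v 2. If mid-point means the middle of the crossover sequence, it is 3 v 3. At study end it is 6 v 0. Four (or three) clusters are never interviewed unexposed.

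**2. Floor of a randomisation test on exposed v unexposed.** With two clusters per size group and one of each size in each half, there are 2³ × 3! × 3! = 288 admissible sequences.
- 4 v 2: the last two positions hold one of 3 × 2 × 2 = 12 equally likely pairs. Smallest p = 1/12 = 0.083.
- 3 v 3: there are 2³ = 8 splits, and the mirror image of each is also admissible. Smallest p = 1/8 = 0.125 one-sided, 2/8 = 0.25 two-sided.

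**3. The general model on two rounds.** The model has three parameters (two round means and the effect) and a design of rank 3, so the effect is identified. Take total variance 1, intracluster correlation ρ, n providers per cluster-round and k clusters exposed at mid-point. All clusters are exposed at the end, so that round's mean is a free parameter, and the end scores only adjust the mid-point comparison:

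Var = (1/k + 1/(6 − k)) × v × (1 − r²), with v = ρ + (1 − ρ)/n and r = ρ/v.

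For n = 10 and ρ = 0.05: v = 0.05 + 0.095 = 0.145, r = 0.345 and v(1 − r²) = 0.128.
- 3 v 3: SE = √(0.667 × 0.128) = 0.292 SD.
- 4 v 2: SE = √(0.75 × 0.128) = 0.310 SD.

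Over n = 5 to 20 and ρ = 0.01 to 0.10 (both assumed; the document gives neither for providers):

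| Quantity | Range |
|---|---|
| SE | 0.20 to 0.43 SD |
| Effect detectable with 80% power, normal | 0.55 to 1.20 SD |
| Effect detectable with 80% power, t on 4 df | 0.73 to 1.59 SD |

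**4. Error rates.** Data were simulated with no effect, 8 providers per cluster-round and ρ of 0.05 to 0.10. The mixed model with cluster-robust standard errors and normal reference values rejected in about 16 to 24% of trials at nominal 5%. A repeat simulation under the same assumptions fell inside that range.

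A t test on the six cluster means at mid-point (4 df; 6 providers per cluster and ρ = 0.05 assumed) held 5%. Its power was 0.17 to 0.18 at 0.5 SD, 0.48 to 0.53 at 1 SD and 0.81 to 0.85 at 1.5 SD.

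**5. Would a baseline round have cured it?** Adding an all-control round at n = 10 and ρ = 0.05 moves the SE from 0.292 to 0.282 (3 v 3) or from 0.310 to 0.299 (4 v 2). The 8 or 12 admissible exposed sets do not change.

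**The case against.** A reader might infer that the trial cannot test a CQI effect on this endpoint at 5% at all. The document does not support that, for these reasons:
- The clusters still waiting at mid-point are genuine pre-exposure observations, compared concurrently with clusters that crossed earlier by randomised order.
- The mixed model is identified, and a 4-df cluster-level test holds its level.
- The p-value floors belong to a randomisation test that the plan does not propose, and only to its binary form. A statistic using time since crossover, which the plan intends to examine as an effect modifier, has 144 distinct allocations (4 v 2) or 48 (3 v 3). Its floor is 1/144 = 0.007 or 1/48 = 0.021.

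Nor is the missing baseline round the cause of the weakness, as step 5 shows. The cause is six clusters and a single round of mixed exposure.

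It is also fair to say that the 5% level is tied to the primary endpoints, that the intention-to-treat rule is written for patients, and that the analysis of a provider endpoint may be set out in an analysis plan not shown. That limits any claim about what will be run. It does not alter the interview schedule, and no analysis plan can supply data that were not collected.

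Finally, relabelling a prespecified endpoint after data collection can look like a retreat. An estimate with an honest interval answers that, since nothing collected is withheld.

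**Conclusion.** The concern holds as a limit on what this endpoint can support. Three or four of six clusters have no pre-exposure provider data, which contradicts the general sentence in Data sources. The only randomised exposure contrast is one round, 4 v 2 or 3 v 3.

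A valid test has about even odds of detecting a 1 SD effect. The general model with clustered standard errors and normal reference values would reject a true null roughly three to five times as often as intended (16 to 24% against 5%). That multiple depends on the assumed provider numbers and intracluster correlations, and on the general model being applied to this endpoint. The cluster counts and the randomisation floors follow from the document's dates and restriction alone, apart from the meaning of mid-point, for which both readings are given.

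The point is minor: the endpoint is secondary and the primary endpoints are unaffected.

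**What to change.** Before analysis, label endpoint (v) exploratory or descriptive. Report mid-point and end scores by cluster and exposure state, and say which date counted as mid-point. Give at most a cluster-level difference at mid-point with a t-based confidence interval on 4 degrees of freedom, and make no confirmatory claim of a CQI effect. In Data sources, limit the statement that all clusters supplied pre-exposure data to the maternal and infant data.

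The cost is a sentence or two and one inferential claim on a secondary endpoint. No further data are needed.
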